### Data collection

#### Primary outcome

The primary outcome will be dental caries experienced in the 2 years post-enrolment on any tooth in either dentition at the dentinal level of involvement, which had been caries free at baseline.

Following informed consent, the dentist at the assessment or extraction clinic will conduct a baseline dental assessment and complete a full dental charting including presence of caries in remaining teeth, presence of dental plaque on upper anterior teeth and include a note of teeth extracted/to be extracted. Dentists making the caries assessment are all experienced paediatric dentists who will have received standardised training from the PI on the level of dental caries to record, that is, lesions that involve the dentine.

At 2 years post-enrolment, dental officers, trained in standardised techniques for the measurement of dental caries, will examine participating children in their School or at a location convenient to the family. The dental officers will be blind to group allocation. Dental caries experience, at the dentinal level of involvement, on any tooth in either dentition will be recorded. All children will be examined using sterilised or single-use mouth mirrors, a standardized halogen lamp (2,000 lux) and cotton wool rolls as needed.

### Secondary outcomes

Families in both groups will be asked to complete a set of three questionnaires at baseline. Parental readiness to change and beliefs about caring for their children’s teeth will be measured by the modified Contemplation Ladder [39]. Parental self-efficacy in relation to the implementation of dental health-related behaviours for the study children will be measured by the Child Oral Health Behaviours Questionnaire [23] and Parenting Self-Efficacy Scale [40] will also be administered. The parental self-efficacy measures [22, 38] will be administered again at 1 year and 2 years post-enrolment. Use of dental services and child oral health behaviours, including dietary behaviours, also will be obtained at baseline, at 1 year and at 2 years post-enrolment [23]. Oral cleanliness will be measured by plaque assessment on the buccal surfaces of upper anterior teeth at dental examinations.

### Health economic analysis

Cost will be measured from a public sector, multi-agency perspective [41–44]. We will fully cost the community-based DR-BNI and prevention in dental practice programme (as compared with costs of usual dental care); record study participant dental service use, primary and secondary care health service use, social care and special educational service use (using a CSRI, (costed using National unit costs); conduct a primary cost-effectiveness analysis (using dental caries rates as our measure of effectiveness); and conduct a secondary cost-consequences study relating costs to a range of consequences spanning measures of dental decay in the participating child, regular dental attendance, parent participation in better oral health behaviours (for example, sugar-free bedtime routine) and school attendance.

### Sample size

The primary outcome variable is measured by a binary variable, taking the value 1 where a child has caries experience after 2 years on any tooth in either dentition, which was caries free at baseline, and 0 otherwise. In a previous clinical trial conducted by two of the investigators in children from deprived areas in Scotland [45], 55 children aged 5 years had extractions for caries at baseline. Of these, 48 (87 %) had additional caries experience 2 years later. Taking this value as an estimate of the outcome in the control group, and setting the minimum clinically significant difference to 20 percentage points (67 % in the test group), with 80 % power and significance level 0.05 gives a minimum sample size of 78 per group. Previous studies and the pilots suggest allowing up to 30 % for dropouts; final sample size becomes 112 children per group.

### Measures

The Oral Health Behaviours Questionnaire (OHBQ) has been developed in a multi-cultural international study to explore parental attitudes and behaviours in relation to child tooth-brushing, use of dietary sugar, dental attendance and to measure parental self-efficacy in relation to tooth-brushing and dietary sugar [23].

The Contemplation Ladder measures readiness to change behaviour (28). The ladder has been modified for this study to address specifically the four recommended behaviours: 1) brush child’s teeth last thing at night and on one other occasion every day, 2) make regular visits to dentist, 3) limit sugar snacks to mealtimes and no more than four times a day, and 4) the ideal drink for children is milk or water. All of these recommendations come from Delivering Better Oral Health [12].

A parental self-efficacy scale will enable the researchers to measure the impact of the intervention on both general parental self-efficacy (29) and parental self-efficacy related to oral health behaviours, which has been used in a previous study with good reliability [23].

### Method of analysis

All statistical analysis plans will be prepared by the trial statistician, and approved by the Chief Investigator, supervising statistician and Trial Steering Group (TSG) before the allocations are released to the trial statistician and comparative data analysis is carried out. The analysis of the primary outcome variable will use logistic regression, adjusted for the stratification variable centre, and possibly other pre-specified variables judged to be potentially related to the outcome. The primary outcome will be analysed on an intention-to-treat (ITT) basis. In addition, a per-protocol analysis will be carried out to test the robustness of the main results to departures from ITT. Protocol deviations will be defined prior to development of the statistical analysis plan. All participants will have any protocol deviations listed and signed off by the Chief Investigator prior to the release of the randomisation codes to the trial statistical team. Sensitivity analyses will be carried out using multiple imputation to investigate the robustness of the analysis to missing primary outcome data.

Secondary outcome variables will be analysed using linear regression for numerical variables, and logistic regression for binary categorical variables, adjusted for centre and pre-specified potential confounders, as in the primary outcome analysis.

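### The covariate rule for the secondary outcomes is borrowed from the primary analysis and so, as worded, does not bring in each outcome's own baseline value

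*Protocol article*

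**What the plan says.** All references are to the protocol article.

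- **Method of analysis, secondary outcomes.** Numerical outcomes get linear regression and binary outcomes get logistic regression, "adjusted for centre and pre-specified potential confounders, as in the primary outcome analysis".
- **Method of analysis, primary outcome.** The logistic model adjusts for centre, the stratification variable, "and possibly other pre-specified variables judged to be potentially related to the outcome". The section also says that analysis plans will be approved before allocations are released.
- **Secondary outcomes.** The parental self-efficacy measures are taken at baseline and "will be administered again at 1 year and 2 years post-enrolment". Service use and child oral health behaviours, including diet, are obtained at the same three times. Oral cleanliness is assessed from plaque at the dental examinations.
- **Primary outcome (under Data collection).** The baseline charting covers the whole mouth, "including presence of caries in remaining teeth, presence of dental plaque on upper anterior teeth". The outcome itself counts only teeth that were free of caries at that charting.

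**The concern.** The protocol sets a rule for choosing covariates in the secondary models, and the rule points back to the primary analysis. By construction that analysis cannot contain a baseline value of its outcome, because every tooth at risk starts caries-free. An analyst who carried the primary covariates across unchanged would compare follow-up self-efficacy or behaviour scores without the baseline score.

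The selection criterion, potential confounding, does not point to the baseline value either. In a randomised comparison, covariates are useful mainly for how well they predict the outcome, and an outcome's own earlier value is usually among the best predictors.

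Precision in the secondary comparisons is at stake. These carry the evidence on the mechanism that the intervention targets, parental self-efficacy and the related behaviours. Randomisation is stratified by centre only, so the design does not balance these baseline scores beyond what chance provides.

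**Working it through.** **1. The plan's own figure.** Inputs from the Sample size section: 87% against 67%, "with 80 % power and significance level 0.05", 30% dropout. Sidedness is not stated, so two-sided is assumed.

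- Pooled two-proportion formula: n = [1.960·√(2·0.77·0.23) + 0.842·√(0.87·0.13 + 0.67·0.33)]² / 0.20² = 68.3, rounded up to 69.
- With continuity correction: (68.3/4)·[1 + √(1 + 4/(68.3·0.20))]² = 78.0, giving 78 per group.
- Dropout: 78/0.70 = 111.4, giving 112 per group.

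Both stated figures reproduce. They use no covariate adjustment, so nothing below changes them.

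**2. Which outcomes have a usable baseline.**

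| Secondary measure | At baseline | At follow-up |
|---|---|---|
| Parental self-efficacy | yes | 1 and 2 years |
| Oral health behaviours, including diet | yes | 1 and 2 years |
| Use of dental services | yes | 1 and 2 years |
| Plaque on upper anterior teeth | yes (charting) | at dental examination |

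**3. Gain for numerical outcomes.** With correlation r between baseline and follow-up, the variance of the adjusted comparison is 1 − r² times the unadjusted variance, so the cut is r². The difference detectable with 80% power at two-sided 0.05, in SD units and by the normal approximation, is

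(1.960 + 0.842)·√(2/n)·√(1 − r²).

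The calculation takes n = 78 evaluable per group from the Sample size section and assumes that the secondary outcomes are as complete as the primary. The documents give no correlation, so r is assumed and shown as a range.

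| r | Variance remaining | Variance cut | Detectable difference (SD) | Power at 0.449 SD | Equivalent unadjusted n per group |
|---|---|---|---|---|---|
| 0 | 1.00 | 0% | 0.449 | 80.0% | 78 |
| 0.3 | 0.91 | 9% | 0.428 | 83.6% | 86 |
| 0.5 | 0.75 | 25% | 0.389 | 89.9% | 104 |
| 0.7 | 0.51 | 49% | 0.320 | 97.5% | 153 |

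The last column is 78/(1 − r²). With all 112 per group evaluable, the detectable difference goes from 0.374 SD to 0.357, 0.324 and 0.267 SD. The proportional gain is the same.

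**4. Binary outcomes.** The factor 1 − r² does not carry over to logistic regression. There, adjustment raises power without shrinking the standard error of the log odds ratio, and the odds ratio becomes conditional on the covariate. A simulation shows the pattern (3,000 trials, 78 per group, risks 87% and 67%, one covariate with an assumed log-odds slope of 1.0 per SD). The mean log odds ratio moved from −1.24 (SE 0.43) to −1.45 (SE 0.47), and power rose from 85.4% to 90.0%. With a slope of 0.5, power rose from 86.3% to 87.8%. These runs illustrate the behaviour of the method and are not predictions for any secondary outcome.

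**The case against.** The strongest reply is that covariate lists belong in the statistical analysis plan, which is not shown. The protocol requires the covariates to be fixed in advance and the plan approved before unblinding. The cross-reference to the primary analysis can also be read as meaning the same approach, not the same list, and a baseline value could be counted among the pre-specified variables. Under randomisation, an analysis without the baseline value is still unbiased, and its standard error already reflects chance imbalance.

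Most of this stands. A reader might infer that the plan commits to follow-up-only comparisons, but no sentence says so: the baseline value is neither named nor excluded. What the reply leaves is that the protocol does state a rule, and the source it points to cannot contain the term that would help most.

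A reader might also extend the point to the primary model, arguing that baseline caries, teeth at risk and age ought to be mandatory there. The documents do not support that. They name none of these variables and exclude none, and leaving further pre-specified covariates to the analysis plan is proper. A fixed list is also debatable. At the planned risks only about 36 evaluable children would be free of new caries (78·0.13 + 78·0.33 ≈ 10 + 26), which limits how many terms the model can carry, and counts of affected and unaffected teeth are likely to overlap.

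**Conclusion.** The point holds as a no-cost improvement to the secondary analyses. As worded, the covariate rule does not bring in each outcome's own baseline value, although that value is collected.

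For numerical outcomes, using it would cut variance by 9% to 49% over assumed correlations of 0.3 to 0.7, with the detectable difference falling from 0.449 SD to between 0.428 and 0.320 SD at 78 per group. For binary outcomes the gain is in power, and its size cannot be derived from the documents.

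A reader might conclude that the trial is wasting precision. That depends on what the analysis plan says and on correlations that the documents do not give, so an actual loss is not shown. The stated 78 and 112 are correct, validity is not in question, and the choice of primary-outcome covariates is a matter for the analysis plan.

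**What to change.** Amend the secondary-outcome sentence in Method of analysis, and carry it into the analysis plan, to say that each secondary outcome with a baseline measure is adjusted for its own baseline value as well as centre. Use analysis of covariance for numerical outcomes, and enter the baseline value as a covariate in the logistic model for binary ones. Any further pre-specified covariates can remain as planned. State alongside this how a missing baseline value is handled, so that the adjustment does not remove children from the analysis.

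The cost is wording only. The article reports the trial as still recruiting, the baseline measures are already scheduled, and analysis plans are to be approved before allocations are released. No change to sample size, visits or data collection follows.

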## Discussion

To our knowledge, no previous randomised controlled trials have been published investigating prevention of dental caries in children who have previously had an extraction in their primary dentition. Those delivering the intervention are dental nurses, reflecting moves to skill mix in dental care, which is, to date, a rare feature in dental trials. The participants are a hard to reach group in which secondary prevention is a challenge. Children scheduled for extractions are less likely to have been taken to attend their dentist for regular preventive treatment. This lack of engagement with dental care makes the children and families scheduled for extraction particularly difficult to recruit to an RCT. Variations in service delivery between sites have also added to the challenges in implementing the Dental RECUR protocol during the recruitment phase.

The protocol has been refined to allow randomisation and intervention delivery to occur at any appointment after enrolment and up to 6 weeks post-extraction. Participants can therefore participate on the trial whilst attending their routine appointments or have the option to schedule an additional appointment if preferred. This design removes some of the barriers to participation associated with attendance at additional appointments, for example travel and parents’ needing to take time off work. The flexibility of the design also allows staff working on the trial to fit trial requirements around existing appointment schedules at their site.

## Trial status

This trial is currently recruiting participants.

## Abbreviations

ASDN: Additional Skills Dental Nurse
CRF: case report form
DR-BNI: Dental RECUR Brief Negotiated Interview
GA: general anaesthesia
GDP: General Dental Practitioner
LA: local anaesthesia
ITT: intention to treat
MI: motivational interviewing
PSE: parental self-efficacy
RA: relative analgesia
TSG: Trial Steering Group
